### 3.4. Treatment during and after This Study Has Ended/Exclusion from This Study and Discontinuation of This Study

If a child is discovered to have severe pathologies such as malignancies of infection that need acute intervention during this study, then the child has to be excluded and treated. After exclusion, the child and their parents have the possibility of us sharing the discovered information (from this study) about their child’s health status as well as if we will recommend seeking medical care. If a child is being treated, we will allow the child to continue being treated. If a child participating in this study has an unexpected negative effect due to the evaluation, either according to the parents or based on the measurements performed, an assessment by the project coordinator (in collaboration with the parents) will be carried out to decide if the child should be excluded. The reason for exclusion will be reported, and it will be decided if it is still safe to continue the study. The child will continue to receive the best possible care when entering this study. 

### 3.5. Insurance

Upon participating in this study, the participants are covered by the Danish patient insurance “Patientforsikringen” and can complain to “Patientklagenævnet” if unsatisfied with this study.

## 4. Ethical Consideration

### Ethics Approval and Consent to Participate

Before the commencement of the project, we applied to the local ethics committee for ethical approval (H-22002997). The study design was evaluated as a cross-sectional non-intervention study, thus not appropriate for evaluation for approval in accordance with local legal law § 2 or registration as a clinical trial. However, we can confirm that all methods and procedures of this study will adhere to relevant national guidelines and regulations. This includes obtaining informed signed consent from all subjects’ legal guardian(s). If subjects and/or the legal guardians refuse to participate, this will be accepted. Regional registration was obtained in accordance with the Danish Data Protection Agency, as stipulated by Danish law J.nr. 2008-41-2240. 5.3 Ethical Considerations.

The clinical evaluation of children will be a standard orthopedic examination. In our experience, this examination does not cause pain or have side effects/complications, and we expect that the children will not experience pain during the examination, except for minor discomfort. This study entails the evaluation and surface scanning of the children’s legs and feet. All procedures are painless and well-known without known potential side effects or inducing radiation via X-rays. Participants in this study will not experience an increase in the risk of complications or side effects. This study will provide normal materials for orthopedic lower extremity evaluation in children. Previous normal materials for such evaluations are based on a smaller international dataset from decades ago, as described earlier. There is a need to explore this further since the demography has changed during the last decades, and the inclusion of children in this study is justified. We believe that children participating in this study, in addition, will gain information about their anthropologic data as well as their foot and pain statuses. Thus, we believe that the benefits outweigh the risks.

## 5. Procedure and Method

### 5.1. Assessments

In this study, we will utilize clinical evaluations, computer-based technology, and PROMs to gain a more holistic understanding of children’s foot problems and their impact on quality of life. 

### 5.2. Clinical Examinations

The clinical examination in this study is based on the prevalence of pathologies in children to obtain data on the normal material of these children. This entails the examination and registration of the following: -Mapping the foot anatomy and pathologies of warts, foot deformities, ingrown toenails, callosities, hallux valgus, metatarsus varus, and the ROM of the subtalar joint and midfoot, hindfoot valgus, navicular height, static foot pressure mapping, and foot type (square, Roman, or Greek) [26].-Mapping the anthropometric data on children’s height and weight, hip range of motion (ROM) (flexion, internal and external ROM [27], the ROM of knee flexion, and the extension ROM of the ankle joint on a flexed and extended knee [27], as well as the femoral anteversion and torsion of the tibia (foot–thigh ankle)). This is evaluated when the child is either standing, prone, or supine in a standardized manner and using a goniometer (see Supplementary).

### 5.3. Patient-Related Outcome Measures (PROMs) and Pain Status

Our endpoints for this study are foot health, pain status, sports activity level, and quality of life. We will evaluate pain intensity and location using the ‘Chili’ score, Wong–Baker and VAS numeric rating scale, and a systematic pain drawing, respectively [28]. We will measure foot health using the validated Danish version of the Oxford Foot Score for Children (OxAFQ) and compare scores with the prevalence of foot pathologies [29]. The OxAFQ is a discriminative and evaluative tool that can differentiate between severe chronic disease and benign fluctuating disease. We will assess activity levels and the Pediatric Quality of Life (PedsQL) questionnaire. The 23-item PedsQL Generic Core Scales are designed to measure the core dimensions of health as delineated by the World Health Organization. These data will be acquired either via REDCAP via a subject’s social security number for the questionnaires, and pain status will be evaluated when a child is examined. The caregiver and child will also be asked if the child has orthopedic and other diseases.

### 5.4. Equipment

We will evaluate the dimensions of a child’s feet [30,31,32] with a 3D scan using the Volumental scanner (Volumental, Stockholm, Sweden) in a neutral stance and when standing on their toes and with foot pressure mapping [33]. The mapping of the quality of footwear and the size of shoes will be evaluated with measurements of shoe width and length using the MFI shoe evaluation tools [30,32,34]. Figure 1 illustrates the 3D scans, foot pressure mapping, and shoe evaluations.

#### 5.4.1. Measurement Procedure for the Foot

The Volumental 3D foot scanner will be used to scan both feet of a child. Eleven foot-anthropometry parameters will be measured: (1) foot length, (2) forefoot width, (3) arch height, (4) instep height, (5) heel width, (6) ball girth, (7) instep girth, (8) ankle wrap, (9) short heel girth, (10) forefoot height, and (11) hallux valgus angle. The Volumental 3D foot scanner and the anchor point of measurement for each dimension can be seen in Figure 1a,b, respectively. The procedure of the 3D foot scan requires that the participants are barefooted during measurement with a time measurement for each subject of approximately three minutes. The examinators use a tablet to interact with the scanner during the foot-scanning process and to show the scan results to the child. The child needs to take off their shoes and socks before scanning and be wearing shorts that are purchased for this study. The child stands on the base platform of the scanner with both feet positioned slightly apart from one another. Bodyweight should be equally distributed between both feet. We will also acquire scans when the child is standing on their toes. The researcher selects the sex and starts the scan. To capture both feet, the scanning process takes 5 s. After the scan is successfully processed, 3D meshes and foot measurements of both feet are displayed to the child. 

#### 5.4.2. Data Collection Footwear

Data are collected from the outdoor shoes that the children wore to preschool on the day of the examination. Parents are not informed ahead of time on which days data will be collected. 

##### Shoe Length

The inside length of the outdoor shoes is measured using an adapted sliding device designed for this purpose Figure 2a. To determine the inside length with a maximum level of precision, we utilize a commercially available In-Shoe Length Measuring Device (LM, 3079/1/2/3/4, reference N° LM 3074/1/2/3). This hand-held device determines the in-shoe length and, hence, the insole length of shoes by measuring the different heel and toe spring values. The device is seen in Figure 2a.

Measurements are conducted on the insole at one-millimeter intervals. The expansion of the measuring device lengthwise is determined by the resistance generated by the material of the heel counter and the reinforcement of the toe tip. We plan to calculate the lengthwise fit of the outdoor shoes by the difference between the actual inside length of the shoe and the length of the foot. The shoe should be at least 10 mm longer than the foot when classifying the shoe as a properly fitting shoe [35].

##### Shoe Width

The width of the footwear will be measured from the widest point on the inside of the shoe by measuring the sole. A measuring device is designed to determine the maximum shoe width and height at the level of the first metatarsal head (FH). To determine the inside length with a maximum level of precision, we utilize a commercially available In-Shoe Width Measuring Device (SWM 3079/1/2, reference N° SWM 3079/1 = adults SWM 3079/2 = children). This hand-held device determines the shoe (joint) width and girth of the completed footwear. Using a loop-type elastic band, the gauge is inserted and fitted to the shoe. The gauge has a brake that can be released once inside the footwear, allowing the instrument to expand transversally and upward until it meets the inner edges of the shoe. This will activate a break and when extracting the gauge, we will determine the width and height of the footwear. The device is seen in Figure 2a.

#### 5.4.3. Foot Pressure Mapping

We will measure one postural static foot pressure mapping using the Sidas pressure posturology platform presscam V5 (SIDAS SAS, Voiron, France). This scanner is a hybrid pressure posturology platform and is powered via a USB cable connected to a computer. This computerized system consists of a floor mat on which an ultra-thin Tekscan sensor of 960 sensor cells (5 mm2 each) is placed. The mat will be calibrated for each child using the child’s weight before each testing session. The child stands barefoot on the mat, and the maximum plantar pressure for the entire foot is obtained in 300 images. Measurement of the total surface area of both feet, the maximal pressure on both feet (g/cm^2^), and the average pressure on both feet will be required. This will allow us to acquire plantar pressure data in the static mode and center of the pressure center. The device is seen in Figure 2b.

## 6. Analyses and Statistics

The design of our study is a cross-sectional examination of a thousand children from the first, fifth, and ninth grades in Danish primary schools. These will be randomly selected by their socio-economic profiles. Our focus will be on analyzing their clinical status, pain levels, foot dimensions, pressure, and footwear. Specifically, we plan to evaluate misalignments, malpositions, deformities, skin and foot hygiene, and the rotational status of the lower leg, as well as the range of motion in the lower extremities of the children. These data will serve as a reference for the demographic of the foot and provide insights into the health of children’s feet. We will measure foot dimensions using 3D scanning techniques on the children’s feet and assess the quality of their footwear by evaluating shoe sizes with scientific measurements. This will help us determine if there is a mismatch between footwear and foot size, which could potentially lead to deteriorating foot health in children. Additionally, we plan to collect data on foot pressure mapping to determine the pressure points on the children’s feet. We will evaluate their pain status based on the anatomical pain location and type using numerical pain rating scales. 

### 6.1. Availability of Data and Materials

The data in this study will be registered and reported in a REDCap database following the GDPR rules of the Danish data protection agency and will be stored for 5 years after this study has ended. The data of each subject will be filled out by the examining podiatrists assisted by the TAP employee directly on paper, which afterward, will be transferred to the REDCAP database by TAP employees with secure internet access to register/record the data of this study directly in the REDCAP database as well as for any of the apparatus used in this study. General information about the children will be collected from the primary caregiver of each patient using the methodology via Aula and REDCap as described in Section 2.1.

All relevant information collected during this study will be passed on to the participating doctors for evaluation, if necessary. Information regarding the patients will be passed on directly to the participating doctors, if necessary, by using “…@regionh.dk” emails or directly, using the REDCAP database to ensure the protection of the data. All transfers of data will comply with and have been approved according to the current GPDR rules. 

All data about the patients will appear pseudo-anonymized using the patients’ ID numbers. Information will be kept on a logged and secure drive in the RegionH intranet system. Information from medical records will not be retrieved, but data to provide information about this study to the parents and inquire about informed consent will be required to contact them by letter, as described in Section 2.1. This information includes name, age, CPR number, gender, address, and email. All information regarding the patients will be protected according to “Lov om behandling af personoplysninger og Sundhedsloven, afsnit 3 ver. patienters retsstilling”. Information regarding this study, and, thus, the patients, will also be passed on to governmental agencies (health authorities and the Danish Data Protection Agency if an inspection of this study is requested). Data will not be transferred to other countries. The dataset for this study has been generated and is under preliminary analyses and is thus not currently publicly available. For further interest, inquiries about the data can be sent to the corresponding author.

### 6.2. Safety Endpoints and Evaluations

This study is initiated by the Orthopediatric Department at Hvidovre Hospital and will be conducted in collaboration with 20 schools at different locations in Region Hovedstaden and Region Sjælland. This study will be evaluated by the Danish Health Authorities, The National Committee on Health Research Ethics, and the Danish Data Protection Agency (Privacy in RegionH). This study will be conducted according to the guidelines described in this protocol. This study (as in any study) will be monitored for adverse reactions, adverse events, serious adverse events, serious adverse drug reactions, and suspected unexpected, serious adverse reactions following the ICH GCP harmonized guidelines, and it will be estimated by the project coordinator if any event that has occurred could be attributable to the test measurements. This will be assessed continuously. The project coordinator will ask the child and parents in case an event has occurred. The parents will be asked to call the hospital if any serious event has occurred. The treating physician will register and categorize the event in the REDCAP database and report the event to the relevant authorities. The categorization of the event will be performed using the investigator’s brochure as a reference. In this study, adverse reactions and adverse events are defined as follows according to the ICH GCP guidelines. 

### 6.3. Statistical Analysis and Randomization 

Three clusters of equally divided children from the 1st grade, 5th grade, and 9th grade will be evaluated. This was chosen to embrace the spectrum of chronological (with different developmental stages) ages in Danish primary schools. The total planned number of included children is a thousand children. The sample size was chosen based on a balance between the desired statistical robustness and the practical constraints of this study. These constraints include available resources, such as funding, staffing, and logistics. This sample size is in line with or larger than similar large-scale, observational studies in pediatric populations [36,37,38], where specific power calculations can be more complex due to the multitude of variables and outcomes being explored. We acknowledge this as a limitation but also believe that the chosen sample size is sufficient to provide meaningful and robust data for the objectives of our study. The schools will be chosen randomly with the measure of crow fly distance and the number of children in the schools (>1000). A school’s socioeconomic status will be registered based on the ‘Socioøkonomisk reference for grundskolekarakterer 2018/2019′ [36]. The normality of the data will be assessed graphically using quantile–quantile and density plots. 

Based on their distribution, variables will be described using either means and standard deviations (for normally distributed data) or medians and interquartile ranges (for non-normally distributed data). Appropriate hypothesis tests will be conducted based on the distribution of the data. These include Student’s t-test and Wilcoxon’s rank-sum test for continuous data. For categorical data, chi-square tests and Fisher’s exact test will be used as appropriate. *p*-values of ≤ 0.05 will be considered statistically significant. Simple bivariate analyses will be conducted to establish initial associations between potential predictor variables and relevant outcome variables. To investigate the associations between pain and lower extremity kinematic and alignment variables, we will use multilevel multivariable logistic regression models, stratified by grade (1st, 5th, and 9th). Examiner ID will be included as a random factor in the models. The statistical analysis will be performed using the newest available version of R [39].

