
## 1. Introduction

The well-being of children, and the health of children’s feet, is a priority for a range of professionals, such as school nurses, pediatricians, general practitioners, pediatric orthopedics, and podiatrists [1,2]. Social inequality impacts general health in an environment of growing social differences in an increasingly fragmented healthcare system and might raise barriers to accessing qualified health care, thus indicating a need for either rehabilitation and preventive actions or information on healthcare issues concerning children’s diseases of the lower extremities and feet, and a study evaluating the need of healthcare services indicates that this might not reach medical consultation [3,4,5,6,7]. Healthy feet are a prerequisite for many physical activities, and painful feet may inhibit children in physical exercise and give a decreased quality of life [8,9,10]. Children can have painful feet for a plethora of reasons, and structural differences may have an impact on pain and level of activity. Parents and grandparents are concerned that children with in-toeing, flat feet, and curly toes may develop pain or disability, and healthcare workers must be able to differentiate between what are merely physiological variations and what may lead to detrimental conditions as a child grows older. Previous studies indicate that children are born with “flat feet’’ [11,12,13,14] and that the longitudinal medial arch is not fully developed until a child is 6–7 years old [15,16]. Therefore, several studies have failed to show that insoles and special shoes in preschool children change the natural history of flat feet [17]. However, studies examining anthropometric parameters of the lower extremities and feet have not been performed in older children, and little is known about how this affects an older child in relation to pain and how this may affect their participation in sports and other physical activities. Children with flat feet may have a reduced quality of life, thus motivating interventions. A recent study indicates that insoles in older children may change the osseous construction of the foot and thus, may prevent painful flat feet in adults [18]. Therefore, insoles may have the potential to prevent painful flat feet in adults and potentially prevent surgery for this condition in adults [19]. For these motivating reasons, the pediatric orthopedics section of the Rigshospitalet and Hvidovre Hospital, the University of Southern Denmark, and the Association of Danish Podiatrists have started a project for the evaluation and screening of children’s feet and lower extremities in Danish primary schools. Wearing shoes can be underestimated concerning the health of children’s feet, but a too-tight-fitted shoe is known to predispose to hallux valgus and lead to foot pain in children [20,21,22]. Studies in the European setting indicate that children in these countries often wear shoes that are too small [23,24]. The effect of shoe fit also impacts the development of pathological diseases such as apophysitis of the calcanei, and simple ingrown toenails and may give rise to deformities, ingrown toenails, or non-specific foot pain [20,22,25]. In this study, we plan to evaluate this using the commercial technology of 3D surface scanning and evaluate the appropriateness of shoe fitting via the measurement of shoe size. The perspective of this study is that we, in the future, will be able to provide recommendations for preventive actions for children for improvement in the care of the health of children’s lower extremities and feet, thus demonstrating the potential for long-term health and societal financial benefits, such as referral to other health services, guidance on sensible footwear, foot care, and hygiene. The purpose of this project is to identify anthropometric parameters that might be preconditions for pain, evaluate for foot diseases and whether they are associated with pain intensity and location, three-dimensional foot dimensions and foot pressure mapping, shoe dimensions, intensity and type of sports activity, and status of quality of life and foot health according to patient-related outcome measures (PROMs). The aim is that we will be able to identify parameters pre-dispositioning for pain, thus providing recommendations for sports activities in relation to the anthropometric conditions of a child as a potential preventive measure for pain. Our purpose with this study is threefold:To make reference material of the demography of the foot, the rotational status, and the range of motion in joints in the lower extremities of children in Denmark to evaluate if these anthropometric parameters in children influence pain status.Examining the prevalence of pain in children as well as exploring the prevalence of pathologies in children’s feet to evaluate if these conditions in children influence pain status.Evaluating the appropriateness of shoe fitting using commercial 3D technology and foot pressure mapping to evaluate if shoe fitting in children influences foot pain status.

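### The first purpose is reference values for growing children, but the stated summaries give skewed measures no outer limit and give sex and age no role

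*Protocol article*

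**What the plan says.** The Introduction lists three purposes, and the first is "To make reference material of the demography of the foot, the rotational status, and the range of motion in joints in the lower extremities". The ethics section states the intended use: "This study will provide normal materials for orthopedic lower extremity evaluation in children". It justifies including children partly by the age and small size of existing normal data.

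Section 6.3 gives one rule for describing variables: "Based on their distribution, variables will be described using either means and standard deviations (for normally distributed data) or medians and interquartile ranges". The choice between the two pairs rests on quantile–quantile and density plots. No centile, reference limit or reference-interval method is named, and the rule names no grouping.

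Grade stratification appears later in section 6.3, attached to the pain analysis: "multilevel multivariable logistic regression models, stratified by grade (1st, 5th, and 9th". The Abstract also mentions stratification by socioeconomic status at group level. On why three grades are sampled, section 6.3 says: "This was chosen to embrace the spectrum of chronological (with different developmental stages) ages in Danish primary schools".

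Sex and age are available. Section 5.4.1 says "The researcher selects the sex and starts the scan", and section 6.1, on the personal details needed, says "This information includes name, age, CPR number, gender, address, and email". Section 3.2 admits children aged 6 to 18 in the three grades. No section gives sex or age a part in the descriptions or the models.

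**The concern.** A reference value is used to judge whether one child's measurement is unusual for a child like that one. This takes outer limits, and limits that refer to comparable children. The stated method falls short on both.

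- **Outer limits.** For a measure judged non-normal, the plan reports the median and interquartile range. That describes the middle half of the children and says nothing about where the unusual values begin.
- **Comparable children.** The article itself says that the grades represent different developmental stages, and it measures lengths, widths and girths that change with growth. If sexes, ages or grades are summarised together, the differences between them become part of the spread. The range is then too wide for each subgroup and centred wrongly for it. A pooled sample can also look non-normal because it is a mixture, which would push a measure towards the median and interquartile range.

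At stake is whether the first purpose can be met for an individual child. The pain models are a separate matter.

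**Working it through.** The article gives no figure to reproduce here: the 1000 children were chosen pragmatically, without a standard deviation or a precision target. The check therefore has two parts: what the stated summaries can deliver, and how much pooling could matter under assumed differences.

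**1. What the summaries deliver**

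- Mean and SD, normal data: mean ± 1.96 SD implies 2.5% and 97.5% limits for whatever group was summarised.
- Median and interquartile range: the 25th and 75th centiles only. No outer limit follows without a further distributional assumption, and this summary is used precisely when normality has been rejected.

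**2. Sexes pooled within a grade**

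Assumptions: equal numbers of each sex, normal data, within-sex SD of 1, means d apart. The documents do not give d.

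- Pooled SD: s = √(1 + d²/4). Upper limit above the pooled mean: L = 1.96·s.
- Share above the limit: 1 − Φ(L − d/2) in the larger sex and 1 − Φ(L + d/2) in the smaller. The target is 2.5% in each.
- Worked case, d = 0.5: s = √1.0625 = 1.031 and L = 2.020. The larger sex gets 1 − Φ(1.770) = 3.8%, the smaller 1 − Φ(2.270) = 1.2%.

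| d (SD) | pooled SD | larger sex above | smaller sex above |
|---|---|---|---|
| 0.2 | 1.005 | 3.1% | 1.9% |
| 0.5 | 1.031 | 3.8% | 1.2% |
| 1.0 | 1.118 | 4.5% | 0.4% |

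The lower limit mirrors this.

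**3. Ages pooled within a grade**

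Assumptions: age uniform over w years, slope b SD per year (neither is in the documents). Pooled SD = √(1 + (bw)²/12), and the oldest and youngest children lie bw/2 either side of the mean.

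| b (SD/year) | w (years) | oldest above | youngest above |
|---|---|---|---|
| 0.1 | 1 | 2.8% | 2.2% |
| 0.25 | 1 | 3.3% | 1.8% |
| 0.5 | 1 | 4.2% | 1.3% |
| 0.5 | 2 | 6.2% | 0.6% |

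**4. Grades pooled**

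This is the literal reading of a descriptive rule with no grouping. Assume three equal grades with means 1 SD apart. Pooled SD = √(1 + 2/3) = 1.291 and L = 2.530. Above the limit: 1 − Φ(1.530) = 6.3% of 9th-graders and 1 − Φ(3.530) = 0.02% of 1st-graders.

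**5. Precision of a parametric outer limit**

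Half-width of the 95% interval, in SD units: 1.96·√(1/n + 1.96²/(2(n − 1))).

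- One grade, sexes pooled: n = 1000/3 ≈ 333 gives ±0.18. If the 5% dropout comes off the 1000, n = 950/3 ≈ 317 gives ±0.19.
- One grade and sex, 50:50 split assumed: n = 1000/6 ≈ 167 gives ±0.26. After dropout, n = 950/6 ≈ 158 gives ±0.27.
- Children expected in one 2.5% tail of a cell: 0.025 × 167 ≈ 4.

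**The case against.** The strongest objection is that this is a condensed article. A breakdown of tables by sex, or a choice of centiles, could well stand in a fuller protocol or analysis plan that is not shown. Section 6.3 nowhere says that the sexes will be pooled, and it lists neither the groups for its two-sample tests nor the covariates of its multivariable models. This stands in part: silence about sex and age is not a decision to leave them out, and the point should not be read as proof that they will be ignored. It does not remove the point, because section 6.3 does state how variables will be described, and for a reference-value purpose that choice is weak as stated.

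A reader might infer four stronger things that the documents do not support:

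- **That grade is the sole stratifier.** Grade is tied to the pain models only, the descriptive rule names no grouping, and the Abstract also mentions socioeconomic status.
- **That the plan's limits misclassify children.** The plan defines no reference limit and no rule for calling a child abnormal. The 10 mm shoe criterion and the measurement-error thresholds serve other ends. The percentages above describe what a later user would get from pooled mean ± 1.96 SD.
- **That mean and SD give no outer limits.** For normal data they do. The gap concerns the median and interquartile range.
- **That the article plans to fill in ages between the grades.** It states the three grades openly and announces no interpolation.

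The objection that the sizes are assumed also stands. No sex difference or growth rate is given, and for rotational status and range of motion the dependence may be weak.

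**Conclusion.** The point holds in a limited form. The first purpose is reference material for clinical use, and the only stated description does not provide it: skewed measures would have no outer limit, and nothing ties the values to sex or age although both are held. This is a weakness of method that is worth correcting. It contradicts no figure in the article.

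The size depends on the measure. At an assumed sex difference of 0.2 SD the distortion is slight; by 0.5 to 1 SD the larger sex exceeds a pooled upper limit roughly 3 to 13 times as often as the smaller (3.83/1.16 ≈ 3.3; 4.54/0.36 ≈ 12.6). Growth-driven measures such as foot length and girths are the likeliest to be affected. These sizes assume normal data, an even sex split and pooled summaries.

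**What to change.** In section 6.3, add that reference values for continuous measures will be reported by grade and sex, conditional on age at examination where the measure depends on age, as centiles (for example the 2.5th, 10th, 50th, 90th and 97.5th) with confidence intervals. Quantile regression or the LMS method within grade and sex would serve; the choice can be left to the analysis plan. Mean/SD or median/IQR can stay as the general summary of the sample.

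The change costs a few sentences and more tables. Sex and age are already held. The article does not say that the examination date is recorded, so the authors should confirm that age can be fixed at the day of examination.

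The statistical price is precision. With about 167 children per grade and sex, the 95% interval of a parametric outer limit is about ±0.26 SD, against ±0.18 SD for a whole grade. About four children fall in each 2.5% tail, so empirical outer centiles would be imprecise; reporting the intervals shows this to the user. Section 6.1 says that preliminary analysis is under way, so the method should be fixed soon.
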